## 2.2 SERIOUS ADVERSE EVENT REPORTING PROCEDURES

With one exception, serious adverse events will be collected and recorded from the date of the post-CRT MRI scan is performed until 30 days after the last dose of chemotherapy is administered.

The only exception to this rule is the recording and reporting of involved surgical resection margins described in section 2.1.4 above.

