#### 4.4.2 SECONDARY ENDPOINTS

- The pCRM rate will be compared between the control and investigation arms.
- The strength of agreement of the reported mrTRG will be evaluated between the site radiologist versus the central radiologist at site initiation and at the end of the feasibility trial.
- Acute toxicity will be recorded to CTCAE v4.0 protocol. The grade 3- 5 adverse events will be compared between the control and intervention arms on an intention to treat basis.
- Early (30 day) and late (up to 12 months) surgical morbidity will be reported according to the Clavien-Dindo classification
- Quality of surgery will be determined by using the mesorectal grading system and a similar system will be used for grading the quality of APE specimens (Pathology appendix). Outcomes will be compared between the control and intervention arms on an intention to treat basis.

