## 10. ASSESSMENT SCHEDULES

Please refer to the assessment schedules below for details of assessments to be performed, timelines and the CRFs to complete (further details relating to CRF completion can be found at the front of the CRF pack).

- Radiological assessment will be performed as per [Appendix 6](#) with synoptic reporting according to the allocated **POST-TREATMENT MRI FORM**.
- Chemotherapy toxicity will be assessed at the end of each cycle during treatment and residual toxicity assessed at the 12-month follow-up visit.
- When surgery is performed, surgical morbidity will be recorded intra-operatively and both early (6 weeks) and late (up to 12 months) surgical complications will be recorded post-operatively.
- **The QUALITY OF LIFE Form** will be completed by all patients at registration. For patients that undergo surgery the QoL forms should be completed again at 1 and 3 years following the completion of CRT. For patients who defer surgery the QoL forms should be completed at 1, 3 and 5 years from the time of CRT completion.
- Adverse events should be recorded from the date of the post-CRT MRI scan until 30 days after the patient's last dose of chemotherapy received during the intervention phase of the trial. Residual toxicity will be assessed at 12 months. Concurrent medications should be recorded at registration and updated from randomization until 30 days after the patient's last dose of chemotherapy. .
- **ANNUAL FOLLOW-UP Forms** should be completed at 12 months from the end of CRT and annually thereafter up to 3 years in those that undergo surgery and up to 5 years in those who defer surgery.

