## **ADVERSE EVENTS AND SERIOUS ADVERSE EVENTS RELATED TO SURGERY**

Surgical adverse events and serious adverse events have been translated into complications. As surgery takes place during the Intervention Phase of the trial adverse events related to surgery should also be recorded on the **ADVERSE EVENTS Form**. Investigators should record on the **ADVERSE EVENT Form** whether the AE is related to systemic chemotherapy or surgery. A list of expected surgical complications is included in Section 2.3 below. Further information relating to early and late surgical complications will be captured on the **SURGICAL MORBIDITY Form**.

Please see section 2.1.4 regarding reporting of involved surgical resection margins (pCRM involvement).

For deferral of surgery the only adverse event of interest is **unsalvageable regrowth** (definition in section 11.3). This will be detected by the MDT during follow up. If it occurs this should be recorded on the **ADVERSE EVENT Form** and it is *definitely related* to deferral of surgery. A **SURVEILLANCE Form** should also be completed.

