### 2.2.1 EXEMPTIONS FROM SAE REPORT SUBMISSION

For this trial, the following events are exempt from requiring expedited notification on an SAE Report Form, but must be recorded in the relevant section(s) of the trial CRFs:

- any event that occurs after 30 days post last dose of chemotherapy that is not an ***AE of special interest*** listed in the section above or considered to be causally related to trial treatment
- Elective hospitalisation and surgery for treatment of locally advanced rectal carcinoma or its complications e.g. bowel obstruction
- Elective hospitalisation to simplify treatment or procedures e.g. central line insertion
- disease progression leading to hospitalization, or prolongation of hospitalization, or death as a result of disease progression

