### SURGICAL MORBIDITY

All of the patients in this trial will have received radiotherapy and chemotherapy prior to surgery, which is believed to increase surgical morbidity. This is of greatest importance for those patients initially managed by deferral of surgery who later require surgery due to tumour regrowth.

Intra-operative and post-operative data will be collected. Post-operative complications will be recorded by clavien-dindo classification (table below). An anastomotic leak is defined as a clinically suspected leak, confirmed radiologically or at re-operation. Severity of anastomotic leakage should be graded according to the impact on clinical management: Grade A anastomotic leakage results in no change in patients management, whereas grade B leakage requires active therapeutic intervention but is manageable without re-laparotomy. Grade C anastomotic leakage requires re-laparotomy.

| Surgical Morbidity: Clavien-Dindo Classification |                                                                                                                                                                                                                                                                                              |
|----------------------------------------------------------------------|----------------------------------------------------------------------------------------------------------------------------------------------------------------------------------------------------------------------------------------------------------------------------------------------|
| Grade 1                                                       | Any deviation from the normal postoperative course without the need for pharmacological treatment or surgical, endoscopic and radiological interventions. Acceptable therapeutic regimens are: drugs as antiemetics, antipyretics, analgesics, diuretics and electrolytes and physiotherapy. |
| Grade 2                                                       | Requiring pharmacological treatment with drugs other than such allowed for grade I complications. Blood transfusions and total parenteral nutrition are also included.                                                                                                                       |

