| Grade 3                                                       | Requiring surgical, endoscopic or radiological intervention.
3a - not under general anesthesia
3b - intervention under general anesthesia                                                                                                                                              |
| Grade 4                                                       | Life-threatening complication (including CNS complications) requiring IC/ICU-management
4a - single organ dysfunction (including dialysis)
4b - multi organ dysfunction                                                                                                                |
| Grade 5                                                       | Death. A serious adverse event (SAE) form must be completed.                                                                                                                                                                                                                                 |

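### The adverse-event window is tied to chemotherapy, not surgery, so it misses late salvage surgery and some poor-responder surgery while covering most control-arm surgery

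*Protocol*

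**What the plan says.** **The window.** Protocol Section 10 states: "Adverse events should be recorded from the date of the post-CRT MRI scan until 30 days after the patient's last dose of chemotherapy", limited to chemotherapy of the intervention phase. The footnotes to the schedules in 10.1, 10.2 and 10.3 repeat this. Appendix 1, Section 2.2 applies it to SAEs: "serious adverse events will be collected and recorded from the date of the post-CRT MRI scan is performed until 30 days after the last dose", where the dose meant is again chemotherapy. It then adds: "The only exception to this rule is the recording and reporting of involved surgical resection margins described in section 2.1.4 above".

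**Surgical events.** Appendix 1, Section 2 explains why these belong on the adverse event form: "As surgery takes place during the Intervention Phase of the trial adverse events related to surgery should also be recorded on the" adverse event form. The same place requires unsalvageable regrowth, which is detected during follow-up, to go on that form.

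**Exemption and deaths.** Appendix 1, Section 2.2.1 waives expedited SAE notification for "any event that occurs after 30 days post last dose of chemotherapy", unless the event is of special interest or judged causally related to trial treatment. Appendix 4 defines Clavien-Dindo grade 5 as follows: "Death. A serious adverse event (SAE) form must be completed". It gives no time limit. On morbidity after prior radiotherapy and chemotherapy, Appendix 4 says: "This is of greatest importance for those patients initially managed by deferral of surgery who later require surgery due to tumour regrowth".

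**Analysis.** Section 4.4.2 states: "The grade 3- 5 adverse events will be compared between the control and intervention arms on an intention to treat basis". Section 14.2.2 describes the tested variable as toxicity and lists acute toxicity under poor responders (mrTRG3-5) only.

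**The concern.** The stated reason for recording surgical events is that surgery lies inside the intervention phase. That holds for control patients who go on to adjuvant chemotherapy. It does not hold for a patient who defers surgery, completes chemotherapy and is operated on for regrowth during later surveillance. By then the window has closed, and only margin involvement is excepted.

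Whether an operation falls inside the window can also depend on its outcome. If a poor responder's complications rule out adjuvant chemotherapy, the last dose is the pre-operative one and the window shut before the operation. The events then least likely to be collected include some of the most serious.

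At stake is the completeness of the safety data from which the TMG and DMEC judge deferral of surgery, in the patients whom Appendix 4 singles out.

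**Working it through.** The plan gives no figure to reproduce; the point rests on timing. Times are in weeks from the end of CRT, without dose delays.

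**Inputs**
- Window end: last dose + 30 days, and 30/7 = 4.3 weeks (Section 10; Appendix 1, Sections 2 and 2.2).
- Control: surgery at weeks 6-12 (Section 8.1), adjuvant start 4-12 weeks after surgery (Appendix 2, Section 1.1), 24-week course.
- Good responders: 24-week course starting within 12 weeks (Section 8.2). I assume week 4 as the earliest start, because the restaging MRI is due at 4-6 weeks.
- Poor responders: surgery 6-12 weeks after pre-operative chemotherapy (Section 8.3).
- Surveillance after deferral: 5 years = 60 months (Section 11.2.1).
- First to last dosing day: CAPOX 7 × 3 + 13/7 = 22.9 weeks; FOLFOX 11 × 2 + 1/7 = 22.1 weeks.

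**Window close = chemotherapy start + time to last dose + 4.3** (sums use unrounded terms)

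| Group | Earliest (FOLFOX) | Latest (CAPOX) |
|---|---|---|
| Good responders | 4 + 22.1 + 4.3 = 30.4 | 12 + 22.9 + 4.3 = 39.1 |
| Control, adjuvant given | 6 + 4 + 22.1 + 4.3 = 36.4 | 12 + 12 + 22.9 + 4.3 = 51.1 |

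- Good responders: at 4.35 weeks per month the window closes at 7.0 to 9.0 months. Surveillance time left is (60 − 9.0)/60 = 85% to (60 − 7.0)/60 = 88%.
- Control: surgery at weeks 6-12 precedes closure at weeks 36-51, so it is inside whenever adjuvant chemotherapy is given.
- Poor responders without adjuvant chemotherapy: the window closes 4.3 weeks after the last pre-operative dose and surgery comes at 6-12 weeks, so it is outside.
- No systemic chemotherapy, any arm: there is no last dose, so no closing date. Section 3.3 offers control adjuvant therapy according to baseline risk features, so such patients can be expected.

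**Passages side by side**
- Section 8.2.2 sends salvage patients to the control schedule, which marks adverse events at surgery and surgical follow-up. The footnote to that row repeats the 30-day limit, so the referral does not reopen the window.
- A death after salvage surgery at, say, month 18 with no further chemotherapy needs an SAE form under Appendix 4 and is not collected under Appendix 1, Section 2.2.
- Unsalvageable regrowth must go on the adverse event form, yet most of the surveillance in which it can be found lies after closure.
- Section 2.2.1 turns on whether salvage surgery is trial treatment. Appendix 1 defines serious adverse reactions on systemic chemotherapy and gives a causality scale for that alone. Section 8.2.2 has a patient who refuses salvage surgery complete a form for stopping trial treatment, which suggests that the surgery does count.
- In the 10.3 schedule as I read it, the adverse-event row is blank at surgery and surgical follow-up. The table may have been misread, so nothing here rests on it.

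**Scale, on assumed values only.** With 90 × 2/3 = 60 intervention patients, assume 30-50% good responders, regrowth in 15-40% of them, 40-80% of salvage operations after closure and a grade 3-5 surgical event in 20-40%. Low: 60 × 0.30 × 0.15 × 0.40 = 1.1 operations, × 0.20 = 0.2 patients. High: 60 × 0.50 × 0.40 × 0.80 = 9.6 operations, × 0.40 = 3.8 patients. None of these rates is in the protocol.

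**The case against.** The strongest reply is that surgical harm has its own route. After regrowth surgery, Section 8.2.2 requires the surgery, surgical morbidity and pathology forms. Section 14.2.2 compares maximum Clavien-Dindo grade between arms in all patients. Margin involvement is reported regardless of the window. Section 2.2.1 waives only expedited notification, still requires recording on the CRFs, and does not cover events related to trial treatment. The DMEC may ask for any analysis (Section 13.4.2). All of this stands and limits the damage. It does not give the TMG and DMEC complete SAE listings, and it does not settle the conflict between Section 2.2 and Appendix 4.

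A reader might infer more than the protocol supports:
- *The grade 3-5 comparison is biased towards the intervention.* This follows only if surgical events count. Section 4.4.2 speaks of adverse events, but directly after a sentence on acute toxicity. Section 14.2.2 says toxicity, and under poor responders only. If drug toxicity is meant, missing surgical events do not bias it. No between-arm SAE test is planned.
- *All salvage surgery is missed.* Surgery within 30 days of the last dose starts inside the window, and chemotherapy given afterwards arguably extends it.
- *The last dose could be the one given with CRT.* Section 10 and the schedule footnotes limit the window to intervention-phase chemotherapy.
- *The window catches only about 15% of regrowth surgery.* The 12-15% of surveillance that it covers is calendar time. The protocol gives no regrowth rate or timing.
- *The loss is all on one side.* The undefined closing date also affects control patients who get no chemotherapy.

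**Conclusion.** The point holds as a defect in safety data collection. Followed as written, the rule gives unequal AE and SAE ascertainment between arms. It leaves SAE reporting to the TMG and DMEC incomplete for late salvage surgery and for poor-responder surgery without adjuvant chemotherapy. It also contradicts the protocol's own reason for recording surgical events and its SAE requirement for post-operative deaths.

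The timing figures rest on the protocol's schedule without delays and on an earliest chemotherapy start at week 4. The number of events lost, and the size of any bias, cannot be derived from the protocol. The primary endpoint, recruitment, is untouched, and the affected comparisons are exploratory. The point is worth correcting, but it does not threaten the trial's main conclusion.

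**What to change.** - In Section 10, the footnotes to 10.1-10.3 and Appendix 1, Sections 2 and 2.2, run AE and SAE collection from the post-CRT MRI to the later of 30 days after the last dose of trial systemic chemotherapy and 30 days after any resection, index or salvage. State that collection reopens at salvage surgery and that the resection rule closes it where no systemic chemotherapy is given.
- State that unsalvageable regrowth is recorded whenever it is found.
- In Section 2.2.1, remove events within 30 days of a resection from the first exemption, so that it agrees with Appendix 4, and include them in the DMEC's SAE report. Say whether salvage surgery is trial treatment.
- Reconcile Sections 4.4.2 and 14.2.2 on whether the grade 3-5 comparison covers drug toxicity or all adverse events, and in which patients. Check the adverse-event row in 10.3.

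The cost is protocol wording and a few extra AE and SAE forms. Early complications are already recorded on the surgical morbidity form, so no visit is added and no treatment rule changes. The intervention arm's event count may rise somewhat, which should be explained when results are reported.

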#### **Control arm versus Intervention arm: good responders (mrTRG1&2)**

- The pCRM involvement rate in the good responders of the control versus intervention arm
- The proportion of patients with unsalvageable regrowth (defined in section 11.3). Greater than 5% unsalvageable regrowth may lead to premature closure of the trial or decision not to proceed to the phase III study.

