### 2.1.4 ADVERSE EVENTS OF SPECIAL INTEREST

These chemotherapy agents are established treatments for colorectal cancer, therefore there are no IMP-related events of special interest.

**All involved surgical resection margins (pCRM involvement) should be treated as adverse events of special interest requiring expedited reporting to the trial office. Information relating to pCRM involvement is captured on the PATHOLOGY CRF, which should be completed at the time the surgical specimen is evaluated and reported. The PATHOLOGY CRF should then be sent to the TRIGGER Trial office as soon as it has been completed and signed and dated by the local Pathologist.**

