**Please ensure that all completed SAE reports are faxed within 24 hours of becoming aware of the event.**

**SAE FAX NUMBER - [name]**

Follow-up of adverse events will continue until all the necessary safety data for the event has been gathered and until the drug-related AE or SAE has either resolved, returned to baseline or stabilised. For fatal or life-threatening cases, follow-up information should be reported as soon as possible. The investigator may be asked to provide follow-up information, discharge summaries, and extracts from medical records as necessary.

Should the investigator become aware of any drug-related SAEs after a patient has been withdrawn from study treatment these must also be reported within the timelines specified above.

The CTIMP Lead and CI (or in nominated individual in their absence) will be responsible for expedited reporting of all SUSARs to the MHRA, REC and Clinical R&D Office no later than 7 calendar days for fatal or life threatening SUSARs, or no later than 15 days for SUSARs which are nonfatal or non-life threatening. Follow up information for death/ life-threatening SUSARs should be provided within 8 days of initial report. For all other SUSARs, follow up report should be provided when the information becomes available.

The Sponsor is also responsible for all submissions of annual reports to the MHRA and REC. Development Safety Update Reports (DSURs) will be prepared in conjunction with the Clinical R&D office.

All SAEs will be reported to the Trial Management Group (TMG) approximately 6-monthly and to the Data Monitoring and Ethics Committee (DMEC) annually.

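### Unsalvageable regrowth, the event behind the 5% closure limit, has contradictory recording rules, no clear expedited route when surgery is not performed, and no stated report to the DMEC between annual reviews

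*Protocol*

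**What the plan says.** **The limit.** Section 14.2.2 (good responders) states: "Greater than 5% unsalvageable regrowth may lead to premature closure of the trial or decision not to proceed to the phase III study". No other safety event in the protocol has a numeric limit for closing the trial.

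**Recording without a time limit.** Appendix 1, section 2 (events related to surgery) says: "For deferral of surgery the only adverse event of interest is" unsalvageable regrowth. It is to be found by the MDT during follow-up, entered on the adverse event form and classed as definitely related to deferral. The notes under the surveillance table in section 11.2.1, which runs for five years, repeat the instruction and add the surveillance form.

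**Recording with a time limit.** Section 10 says: "Adverse events should be recorded from the date of the post-CRT MRI scan until 30 days after the patient's last dose of chemotherapy". Appendix 1, section 2 gives the same window for all adverse events. Section 2.2 says that "serious adverse events will be collected and recorded from the date of the post-CRT MRI scan is performed until 30 days after the last dose"; the dose meant is chemotherapy. It then allows a single departure: "The only exception to this rule is the recording and reporting of involved surgical resection margins described in section 2.1.4 above".

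**Expedited reporting.** Appendix 1, section 2.1.4 names a single class of event: all involved surgical margins "should be treated as adverse events of special interest requiring expedited reporting to the trial office". Section 2.2.1 exempts events later than 30 days after chemotherapy unless they are of special interest or causally related to trial treatment. It also exempts "disease progression leading to hospitalization, or prolongation of hospitalization, or death as a result of disease progression".

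**Committees.** Under Appendix 1, section 2.4, SAEs go to the TMG "approximately 6-monthly and to the Data Monitoring and Ethics Committee (DMEC) annually". Section 13.4.2 has the DMEC meet annually, or more often if that is considered appropriate.

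**The concern.** The event that can close the trial should have the clearest reporting path in the safety appendix. Here a site has one instruction to record it whenever it is found and another that ends recording within the first year, with an exception clause that leaves this event out. An involved margin after surgery goes promptly to the trial office. A regrowth judged beyond surgery yields no specimen and no pathology form, and nothing in the appendix clearly gives it the same treatment.

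Two things are at stake. One is complete and prompt counting of an event for which one or two cases decide whether 5% is passed. The other is whether the independent committee hears of those cases while further patients are being offered deferral.

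**Working it through.** The 5% is stated without a derivation, so there is no figure of the plan's own to reproduce. The check covers timing, routes and counts.

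**1. When the window closes.** Inputs: chemotherapy starts within 12 weeks of CRT and lasts 24 weeks (section 8.2); recording ends 30 days after the last dose.
- Good responder, latest planned start: (12 + 24) × 7 + 30 = 282 days = 40.3 weeks. 282 / 30.44 = 9.3 months after CRT.
- Good responder starting at week 4 (assumed, the earliest planned restaging MRI): (4 + 24) × 7 + 30 = 226 days = 7.4 months.
- Poor responder who later defers (section 8.3: start at week 12, 12 weeks of chemotherapy, MRI 6 weeks later, then 12 more weeks at once): (12 + 12 + 6 + 12) × 7 + 30 = 324 days = 10.6 months.

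**2. How much surveillance lies beyond it.** Section 11.2.1 schedules visits at 6, 9, 12, 15, 18, 21, 24, 30, 36, 42, 48, 54 and 60 months, with MRI at 6, 9, 12, 18, 24, 36, 48 and 60. After 9.3 months come 11 of 13 visits, 6 of 8 MRIs and 1 − 9.3/60 = about 85% of the period. For the poor responder who later defers, the share is 1 − 10.6/60 = about 82%.

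**3. The two forms of the event.** Section 11.3 defines unsalvageable regrowth as progression after deferral in which either surgery is not performed because an involved margin is inevitable, or the margin is involved when surgery is attempted.

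| | Margin involved at attempted surgery | Surgery not performed |
|---|---|---|
| Special interest (App. 1, 2.1.4) | Yes, sent as soon as the pathology form is complete | Not listed |
| Exception to the window (2.2) | Yes | No |
| Late-event exemption (2.2.1, first bullet) | Does not apply | May not apply, if deferral counts as trial treatment |
| Disease-progression exemption (2.2.1, last bullet) | Special-interest rule still applies | May apply if progression leads to hospitalisation or death |

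For the right-hand column the bullets of 2.2.1 can point in opposite directions. The causality scale in Appendix 1, section 2.1.3 does not settle it, because it is written for systemic chemotherapy only.

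**4. Time to the DMEC.** Forms reach the trial office within one month (section 12.5). From there, no rule sends a regrowth case to the DMEC. The only scheduled routes are the annual SAE listing and the annual meeting, so the longest wait by default is about 12 months.

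**5. How many cases pass 5%.** With 2:1 allocation of 90 patients, 60 are in the intervention arm. The share with mrTRG 1–2 is not given. Section 1 speaks of up to 30% with complete or near-complete response; I take 30% as a stand-in, with a range of 20–60%.

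| Assumed share | Eligible for deferral | Fewest cases above 5% | Chance at true rate 2% | Chance at true rate 5% |
|---|---|---|---|---|
| 20% | 12 | 1 (8.3%) | 21.5% | 46.0% |
| 30% | 18 | 1 (5.6%) | 30.5% | 60.3% |
| 40% | 24 | 2 (8.3%) | 8.3% | 33.9% |
| 50% | 30 | 2 (6.7%) | 12.1% | 44.6% |
| 60% | 36 | 2 (5.6%) | 16.2% | 54.3% |

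The chances are exact binomial tails; for 18 patients, 1 − 0.98^18 = 0.305. In general one case is enough up to 19 patients (1/19 = 5.3%), and two are needed from 20 to 39 (1/20 is not above 5%; 2/39 = 5.1%).

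**6. Patients entering between reviews.** 90 patients over the 24-month maximum is 3.75 a month. 3.75 × 12 × 2/3 × 0.30 = 9 good responders a year on average, or 6 to 18 over shares of 20–60%.

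**The case against.** Much can be said for the protocol.

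- A reader might infer that regrowth simply falls outside adverse event recording. The documents do not support that. Regrowth during chemotherapy is foreseen (Appendix 1, section 2 and Appendix 2, section 1.2 read together) and lies inside the window. The specific instructions in Appendix 1, section 2 and section 11.2.1 have no end date. A surveillance form is also due at a confirmed or equivocal diagnosis. The fault is unreconciled wording.
- A reader might infer that the event has no expedited route. One form of it already has one through the margin rule.
- Section 2.2.1 keeps late events reportable if they are related to trial treatment. Section 7.5.2 lists choosing surgery despite a complete response among the reasons for discontinuing trial treatment, which suggests that deferral counts as such. SAE status is therefore unclear rather than excluded.
- Expedited in section 2.1.4 means sending the pathology form once it is complete; it is not the 24-hour SAE report. The contrast with a form due within a month is modest.
- A one-year delay is the worst case. It comes from the DMEC's meeting schedule, so listing the event in section 2.1.4 would not by itself shorten it. The DMEC may meet more often and request analyses, collaborators may write to its chair, and the TMG meets at least four times a year.
- A reader might infer from section 13.4.2 that the DMEC can act only on a very high standard of proof from the randomised comparison. The section first gives it a general remit on data and safety.
- The limit says closure may follow, so it is discretionary.

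These points narrow the matter. They do not reconcile the window and its single exception with the follow-up instructions, settle the route when surgery is not performed, or tie any report to the 5%.

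**Conclusion.** The point holds as a conflict in the reporting rules with a missing link to the DMEC. About 85% of surveillance for a good responder starting chemotherapy at week 12 lies after the stated recording window, while two other places require the event to be recorded then. When surgery is not performed, expedited reporting depends on which bullet of section 2.2.1 a site applies. No report to the DMEC is prompted by a case or by passing 5%.

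The size rests on an assumed good-responder share, on all eligible patients deferring, and on taking those patients as the denominator. At 30%, one case passes the limit; with 20 to 39 patients, two do. A single late or unreported case can therefore decide whether the limit is seen to be passed.

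It does not follow that the limit cannot protect patients, or that a year's silence is the expected course. This should be corrected at the next amendment; it does not call the conduct of the trial into question.

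**What to change.** By amendment:

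1. In Appendix 1, section 2.1.4, list unsalvageable regrowth, expressly including cases where surgery is not performed, as an event of special interest. Give it the same expedited report to the trial office as an involved margin, for the whole surveillance period.
2. In Appendix 1, section 2.2, name it as a second exception to the window. Adjust the window statements in section 10 and Appendix 1, section 2 to match, and say in section 2.2.1 that the disease-progression exemption does not cover it.
3. In section 13.4.2, state that each confirmed case goes to the DMEC when it is reported, with the running count over patients deferring surgery, and that passing the stated 5% prompts DMEC review.

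The third change is the one that shortens the wait; the first two secure the count. The limit itself and patient management stay as they are. The cost is a few paragraphs of text and a small number of extra expedited forms.
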